## PARTICIPATION AND ADHERENCE

The expected benefits will be explained to participants in the intervention group to reduce dropouts and maintain good adherence to the program. The distribution of training sessions throughout the day will minimize fatigue and contribute to adherence. Adherence to training sessions will be monitored daily with specific records, as well as the reasons for non-completion of any sessions.

## STATISTICAL ANALYSIS

Groups will be compared using Student's t-test for continuous variables (or its nonparametric equivalent, the Mann-Whitney test), and chi-square test for categorical variables. The effect of training on outcome variables will be analyzed according to the principle of "intention-to-treat." The effect of training on the primary outcome variable, the proportion of patients who recover the Katz index at 3 months, will be analyzed using univariate and multivariate logistic regression. The effect of training on the recovery of other functional status scales will be analyzed similarly. The change in functional status from admission to discharge and 3 months will be classified as improvement if the number of independently performed ADLs increases or deterioration if the number decreases. Differences between groups will be analyzed using the chi-square test for linear trend. The effect of training on these functional scales as continuous variables will be analyzed using repeated measures analysis of variance (ANOVA) with two factors (between-subjects group and within-subjects time). The consistency of differences between the intervention and usual care in subgroups defined by age, frailty, presence of delirium, and baseline functional status will be analyzed using multivariate logistic regression with normal and ordinal models.

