#### 129        RANDOMIZATION

130        Randomization will be conducted in blocks of four weeks to avoid overlapping participants in both  
 131        groups. Patients admitted over a four-week period will be assigned to a single group (IG or CG). There  
 132        will be a one-week period without inclusion to discharge patients included in the previous weeks, and  
 133        then another four-week block will begin to assign the next group.

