## MEASUREMENT OF VARIABLES

### Primary Variable:

The proportion of patients who, at 3 months post-hospital discharge, recover the Katz index they had two weeks before admission (baseline) will be measured. The Katz index (Katz S. JAMA 1963; 185:914-919) measures the number of Activities of Daily Living (ADLs) performed independently, including bathing, dressing, toileting, transferring from bed to chair, continence, and feeding. For each ADL, a score of 1 is given if performed independently and 0 if any assistance from another person is required. The range is from 0 to 6.

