### Measurement of Secondary Variables:

The Barthel Index assesses 10 items (feeding, bathing, dressing, grooming, bowel control, bladder control, toileting, transferring from bed to chair, ambulation, and stair climbing), with a range from 0 to 100 in 5-point intervals. A lower score indicates greater dependency (Mahoney F. Md Med J 1965; 14:61-65). The Functional Ambulation Classification (FAC) scale (Holden MK. Phys Ther 1984; 64:35-40) assesses walking ability in 6 levels: 0 unable to walk; 1 walks with substantial assistance from one person; 2 requires slight physical contact from one person; 3 walks independently but needs supervision from one person; 4 walks independently on level ground but cannot negotiate stairs; and 5 walks independently on level ground and stairs. These three scales (Katz, Barthel, and FAC) will be measured at 4 time points: 2 weeks before admission (baseline), at admission, at discharge, and at 3 months. The Short Physical Performance Battery (SPPB) (Guralnik JM. J Gerontol 1994; 49:M85-94) assesses the ability to perform three tasks (balance, gait speed, and chair stands) with a total score ranging from 0 to 12. Balance is evaluated by having the participant stand for ten seconds in three different positions: feet together, semi-tandem, and tandem. One point is awarded for each successfully performed position, with a range from 0 to 4. Gait speed is assessed by timing the participant walking 4 meters with or without the use of a cane or walker. Scores range from 4 (less than 4.8 seconds) to 0 (unable to perform). Chair stands measure the time it takes to stand up from a chair five times as quickly as possible without using the arms. Scores range from 4 (less than 11.2 seconds) to 0 (more than 60 seconds or unable to perform). These measures will be taken at admission and discharge. All outcome variables will be assessed by the same properly trained investigator who is not involved in the intervention. An investigator who did not participate in the training will conduct a telephone follow-up at three months post-discharge with the participant or caregiver (from both groups) to assess the functional status of ADLs (Katz index, Barthel index) and ambulation (FAC).

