## SAMPLE SIZE

Calculated by estimating the proportion of patients who recover their baseline Katz index at 3 months post-hospital discharge. In our AGE CAR study, in the control group, 40% of patients recovered their baseline Katz index at 3 months. With the current intervention, we expect that 60% will recover the Katz index at 3 months. Therefore, with a statistical power ( $1-\beta$ ) of 80% and a significance level ( $\alpha$ ) of 0.05 (two-tailed), we need to analyze a total of 188 patients, rounded to the nearest "10," which is 190 patients. Hospital mortality in our unit is approximately 12%, and assuming a 20% loss to follow-up, we will need to include 252 patients, 126 in the intervention group and 126 in the control group.

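### Katz change is tested only by its direction, without the admission score as covariate, so this secondary test of ADL change has less power than the data allow

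*Protocol*

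**What the plan says.** The Katz index counts activities done independently: "The range is from 0 to 6". Under Measurement of Secondary Variables, Katz, Barthel and FAC "will be measured at 4 time points: 2 weeks before admission (baseline), at admission, at discharge, and at 3 months".

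In Statistical Analysis, change from admission to discharge and to 3 months "will be classified as improvement if the number of independently performed ADLs increases or deterioration if the number decreases". A middle category of no change is implied but not named. The test follows: "Differences between groups will be analyzed using the chi-square test for linear trend". No covariate is mentioned.

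Two neighbouring analyses matter here:
- "The effect of training on these functional scales as continuous variables will be analyzed using repeated measures analysis of variance (ANOVA) with two factors", the factors being group and time.
- The primary outcome, recovery of the pre-admission Katz at 3 months, is handled apart from both: it "will be analyzed using univariate and multivariate logistic regression".

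The statistical analysis plan is not at hand. The point concerns only the method that the protocol itself names.

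**The concern.** Cutting a seven-level score to the sign of its change has two costs. A gain of one activity counts the same as a gain of five. The category also depends on where the patient starts: a patient at 6 on admission cannot improve, one at 0 cannot deteriorate, and low starters tend to rise more than high starters whatever the treatment. A trend test on the categories leaves that variation in the noise, although the admission score is on file for every patient.

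The analysis is secondary, but it has some weight. The Hypothesis includes benefit at discharge, and Background (AGECAR Study) says the group's previous trial saw its effect in the numbers improving and worsening in ADLs between admission and discharge. A weak test there could miss an effect of the kind this trial was built to extend.

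**Working it through.** **The plan's own figure.** The protocol gives no power or sample size for the trend test. Its 188 belongs to the primary outcome and reproduces with the unpooled formula: (1.960 + 0.842)² × (0.4×0.6 + 0.6×0.4) / 0.2² = 94.19 per arm, or 188.4 in total. It says nothing about the test discussed here.

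**Inputs from the protocol.** Katz 0–6; 252 patients, 1:1; 12% hospital mortality; 20% loss to follow-up; two-sided 5% level. Assessed at discharge: 252 × 0.88 = 221.8, taken as 220. Assessed at 3 months: 252 × (1 − 0.12 − 0.20) = 171.4, taken as 170.

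**Inputs assumed.** Latent normal function at admission and follow-up, latent correlation 0.3, 0.5, 0.7 or 0.85, cut into Katz 0–6 with 20% of patients at each end on admission (so 40% start at the floor or ceiling). Mean recovery is 0.3 SD in both arms. Treatment effects of 0.50, 0.44, 0.36 and 0.27 SD were chosen so that the trend test has roughly 66–70% power. Patients are independent.

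**Tests compared.** Trend: (n − 1)r² between arm and sign of change. ANOVA: with two time points, the group-by-time test equals a t-test of change. Adjusted: linear regression of follow-up Katz on arm and admission Katz.

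**Power at n = 220 (3,000 trials per row).**

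| Katz correlation, about | Trend | ANOVA change | Adjusted | Gain over trend | Gain over ANOVA |
|---|---|---|---|---|---|
| 0.25 | 69% | 78% | 94% | 25 | 16 |
| 0.43 | 68% | 78% | 91% | 23 | 13 |
| 0.62 | 70% | 80% | 88% | 18 | 8 |
| 0.78 | 67% | 78% | 84% | 17 | 6 |

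The Monte Carlo standard error is under 1 point (for example √(0.85×0.15/3000) = 0.65 points); repeat runs put the last adjusted figure at 84% or 85%. At n = 170 the trend test has about 55–57% and the adjusted analysis about 86, 82, 78 and 75%.

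**Second set of assumptions.** 95 per arm; latent SD 2.2, rounded and clipped to 0–6; correlations 0.4 to 0.8.
- Trend test: 50–59%.
- The same three categories adjusted for admission Katz: 57–66%.
- ANOVA change: 62–74%.
- Full Katz adjusted for admission Katz: 75–83%.

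Adjusting the three categories alone recovers only about 3–11 points, so most of the gain needs the full scale.

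**Admission imbalance, no treatment effect, n = 220.** One arm is shifted by 0.25 SD, about 0.5 Katz points, at admission.
- *The shift regresses toward the mean at the patient-level correlation.* The trend test rejects in roughly 14–16, 11, 8–10 and 6–8% of trials as the correlation rises. The ANOVA rejects in 6–16%. The adjusted analysis stays near 5%.
- *The shift persists to follow-up.* The trend test rejects in 5–6%. The adjusted analysis rejects in about 9% at the highest correlation and 24–28% at the lowest.

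With no imposed imbalance, all the tests reject at about 5%.

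**The case against.** The strongest reply is that the trend test does not stand alone. The ANOVA in the next sentence uses the full scale, so the size of a change is not lost from the plan as a whole. This stands: the fair measure of what is gained is 6–16 points over the ANOVA as well as 17–25 over the trend test. It does not remove the point, because the ANOVA does not adjust for admission score and the protocol does not say which analysis decides the conclusion on ADL change.

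It is also true that this is a supporting analysis. The primary outcome is modelled separately, and Katz change from admission is not among the listed secondary objectives. Testing the categories also keeps the result comparable with the previous trial, which reported patients who improved and worsened, and needs no proportional-odds assumption.

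Two stronger readings are tempting and are not supported:
- A reader might infer that admission Katz is ignored. It is not: it is the value from which change is defined. It is only not a covariate.
- A reader might infer that any admission imbalance biases the trend test and that adjustment cures this. Under individual randomisation a gap of 0.25 SD or more is uncommon (standard error √(2/110) = 0.135 SD; 0.25/0.135 = 1.85; about 6% of trials), and the overall error rate stays near 5%. Here whole four-week admission periods share one arm, which makes imbalance more likely. But a seasonal or case-mix difference between periods may persist rather than regress, and then it is the adjusted test that is misled. The protocol gives nothing to choose between the two cases.

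**Conclusion.** The point holds as a loss of power in a secondary analysis. Under the assumptions above, power at discharge is about 68% for the trend test, 78–80% for the planned ANOVA and about 85–94% for full Katz adjusted for admission Katz. The direction is the same under both sets of assumptions tried; the exact gain depends on a Katz distribution, correlation and effect that the protocol does not give.

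Three limits apply. The power figures come from linear regression on admission Katz alone. Proportional-odds regression was checked in only 150 trials per setting, at smaller effects (61–71% against 58–70% for the linear model, standard error about 4 points). Patients were taken as independent, and neither the trend test nor the proposed model accounts for allocation by four-week block.

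Bias is not a reason for the change. A regressing imbalance can raise the trend test's false-positive rate to about 7–16%; a persisting one leaves it near 5% and affects the adjusted test instead.

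**What to change.** In Statistical Analysis, replace the sentence naming the chi-square test for linear trend with wording to this effect: *Katz at discharge and Katz at 3 months (0–6) will each be compared between groups by ordinal (proportional-odds) logistic regression adjusted for admission Katz and pre-admission Katz, and the common odds ratio with its 95% confidence interval will be reported.* Keep the percentages improved, unchanged and worse as a descriptive table.

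The cost is one sentence and a slightly longer program. No patients, visits or data are added, and the section already names ordinal logistic models for the subgroup analyses. The small downside is reliance on the proportional-odds assumption and a less direct comparison with the previous trial's categories, which the descriptive table partly preserves.
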